#### C. Cessation.

The analyses of the primary outcome on self-reported 14-days PPA at six months follow-up will follow the intention-to-treat (ITT) principle, assuming that all non-respondents are currently smoking or using nicotine. Data will be analyzed using a generalized linear mixed model (GLMM) to account for clustering, recognizing that youth participants within the same municipality may be more similar to each other than to participants from other municipalities. Results will be presented in a table as odds ratios (ORs) for 14-day PPA at six months after the targeted quit date, with corresponding 95% CIs. A p-value < 0.05 will be considered statistically significant.

Secondary outcomes, including short-term self-reported abstinence, continuous self-reported abstinence, and validated 14-days PPA at six months follow-up, will be analyzed using the same GLMM approach as for the primary outcome and presented in tables as ORs with corresponding 95% CIs. In addition, a table will present and compare the baseline characteristics of all youth participants between the intervention and control groups, including age, educational level, type of nicotine product used, and follow-up participation rates.

Given the high degree of data completeness in STOPbasenwe intend to employ a complete case analysis, excluding patients with any missing values in the included variables from the analysis (listwise deletion). Consequently, a sensitivity analysis using an as-observed approach will be conducted, including only participants with a valid follow-up. Sensitivity analyses will be performed using the final adjusted model from the main analyses. This approach builds on the assumption that data is Missing Completely At Random (MCAR). However, when it comes to smoking status, data are more likely to be Missing Not At Random (MNAR). Therefore, if necessary, considering the number of missing values and loss to follow-up, a sensitivity analysis using a chained multiple imputation model will be conducted based on the final adjusted model in the main analyses.

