### Sample size calculations

The sample size calculations are based on the expected difference in self-reported point prevalence abstinence (PPA) six months after the targeted quit between the intervention and control groups. Based on data from STOPbasen and international literature [14,19], the abstinence rate under the intention-to-treat analysis (ITT) approach is estimated to be 23% in the control municipalities and 34% in the intervention municipalities. The power calculations incorporate an intraclass correlation coefficient (ICC) of 0.05 to account for expected similarities among participants within clusters. This adjustment reflects the likelihood that young people within the same municipality receive support from the same youth coach/cessation counselor and are exposed to the same contextual environment (e.g., schools or other youth arenas). Despite extensive follow-up procedures, a 20% loss to follow-up is expected and is included in the sample size estimation [20]. Based on these assumptions, each municipality must include at least 27.8 youth participants in cessation activities during the entire intervention year, a total of 1,526 youth participants.

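### The cessation analysis does not reconcile listwise deletion with counting non-respondents as users, and it answers a stated MNAR concern with an imputation method that in standard form assumes MAR

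*Protocol article*

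**What the plan says.** All the analysis statements are in the Protocol article, Data analysis plan, C. Cessation.

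- **Primary rule.** Self-reported 14-day abstinence at six months is analysed by ITT, "assuming that all non-respondents are currently smoking or using nicotine", in a generalized linear mixed model.
- **Complete-case rule.** Citing the completeness of STOPbasen, the investigators "intend to employ a complete case analysis, excluding patients with any missing values in the included variables". The sentence names no analysis and does not say whether the outcome is one of those variables.
- **Respondents only.** As a stated consequence, "a sensitivity analysis using an as-observed approach will be conducted, including only participants with a valid follow-up".
- **Mechanism.** "This approach builds on the assumption that data is Missing Completely At Random (MCAR"). For smoking status, however, "data are more likely to be Missing Not At Random (MNAR").
- **Response to MNAR.** For that reason, and only if the amount of missing data is thought to make it necessary, "a sensitivity analysis using a chained multiple imputation model will be conducted based on the final adjusted model in the main analyses".

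Under Sample size calculations, "a 20% loss to follow-up is expected". The same section gives ITT abstinence of 23% (control) and 34% (intervention), and a target of 1,526 participants.

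**The concern.** There are two separate problems.

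**The scope of listwise deletion is not stated.** Counting non-respondents as users keeps everyone in the analysis. Deleting anyone with a missing value removes people from it. If the outcome is among the included variables, the first rule never operates. If only covariates are meant, the ITT set still loses anyone with an incomplete covariate. Two analysts could read this section and produce different primary analysis sets for the outcome on which the trial was sized.

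**The response to MNAR does not follow from the concern.** The plan says missingness probably depends on the unobserved smoking status and then, as the remedy, proposes chained multiple imputation. Unless an explicit departure is built in, that method assumes missingness depends only on observed data. It therefore cannot show how sensitive the result is to the mechanism the plan considers likely.

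**Working it through.** **1. Context: the plan's own sample size.** Inputs are 23% v 34%, ICC 0.05, 20% loss and 55 municipalities (27 and 28). The article states no power, so power is assumed. The test is taken as two-sided at 0.05.

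- At 80% power: 264 per arm before clustering. Design effect 1 + (27.8 − 1) × 0.05 = 2.34. Total 2 × 264 × 2.34 / 0.80 ≈ 1,544, which is 1.2% above 1,526.
- At 85% power: 301 per arm. Analysed cluster size with 28 clusters is 301 × 0.95 / (28 − 301 × 0.05) = 22.08. Dividing by 0.80 gives 27.6 per municipality, or about 1,518 in 55.

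The stated 1,526 is close to both and is not disputed here.

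**2. The two rules under the plan's figures (equal 20% loss, clustering ignored).**

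- Non-respondents as users: 23% v 34% on 1,526. OR = (0.34/0.66) / (0.23/0.77) = 0.5152 / 0.2987 = 1.72.
- Listwise deletion including the outcome: respondent rates are 0.23/0.80 = 28.75% and 0.34/0.80 = 42.5%, on 1,526 × 0.80 ≈ 1,221. OR = (0.425/0.575) / (0.2875/0.7125) = 0.7391 / 0.4035 = 1.83.

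**3. The same comparison with unequal loss.** These splits are assumed and are not in the document. Scored rates are held at 23% and 34%, so the OR with non-respondents as users stays at 1.72.

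| Loss, control / intervention | Respondent rates | Complete-case OR |
|---|---|---|
| 30% / 10% | 32.9% v 37.8% | 1.24 |
| 25% / 15% | 30.7% v 40.0% | 1.51 |
| 20% / 20% | 28.75% v 42.5% | 1.83 |
| 15% / 25% | 27.1% v 45.3% | 2.24 |
| 10% / 30% | 25.6% v 48.6% | 2.75 |

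**4. What the planned analyses cover.** Counting all non-respondents as users is itself one MNAR assumption: zero abstinence among them, in both arms. Unadjusted imputation is the MAR point. If it had no useful predictors, it would give non-respondents the respondents' rate in their own arm, so OR 1.83 at equal 20% loss. Nothing is planned between these points or with a different assumption in each arm. The two mixed corners show what is left out:

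- Intervention non-respondents all users, control at MAR: 34% v 28.75%. OR = 0.5152 / 0.4035 = 1.28.
- Control non-respondents all users, intervention at MAR: 42.5% v 23%. OR = 0.7391 / 0.2987 = 2.47.

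These are limits, not forecasts. With the same assumption in both arms the end points are only 1.72 and 1.83.

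**The case against.** The strongest defence is that a coherent reading exists. The rule for non-respondents is tied to the primary outcome by name, and the respondents-only analysis is labelled a sensitivity analysis. Once non-respondents are coded as users, no primary outcome is missing, so deletion could touch only covariates. This largely stands. A reader might infer that the plan deletes non-respondents from its primary analysis, or that its rules are flatly incompatible. The text never says the former, and the covariate reading avoids the latter. But the article does not state that reading. The sentences that follow concern follow-up and smoking status, which point to the outcome, and the covariate reading still breaks the ITT set.

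Four further inferences are tempting and not supported:

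- **That high STOPbasen completeness contradicts 20% loss.** Baseline items are registered in STOPbasen, while six-month status comes from phone calls by a research assistant. Complete baseline data and incomplete outcomes can coexist.
- **That no planned analysis is MNAR.** The primary rule is one, at an extreme. What is missing is the rest of the range, and differences by arm.
- **That follow-up differs by design, so the primary rule will create a false effect.** Unequal response would bias that rule, but six-month contact is described alike for both arms. The extra post-course survey in the intervention arm is not shown to alter six-month response, and follow-up rates by arm are already to be tabulated.
- **That the two rules give very different answers.** At the plan's equal 20% loss the gap is modest.

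It is also fair that imputation details belong in an analysis plan not shown here, and that the imputation is only a conditional sensitivity analysis. The point therefore rests on what the article states: a deletion rule with no stated scope, and an MNAR concern met by a method that does not address it.

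**Conclusion.** The point holds in a limited form and should be fixed. The primary rule for missing outcomes can be identified, but the deletion sentence is not reconciled with it, and either reading of that sentence conflicts with the ITT label. With the plan's rates and equal 20% loss, ignoring clustering, the consequence is an OR of about 1.72 on 1,526 participants against about 1.83 on about 1,221. The wider complete-case range of 1.24 to 2.75 depends on assumed losses of 30% and 10%, in either direction.

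The step from MNAR to standard chained imputation is wrong as stated. Apart from the single extreme of the primary rule, applied alike in both arms, no planned analysis explores MNAR departures or departures that differ by arm. None of this shows that the primary estimate will be biased. It shows that the analysis set is open to interpretation and that the stated sensitivity analyses do not test the assumption the plan itself doubts.

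**What to change.** 1. **State one primary rule.** The primary analysis includes all consenting enrolled participants, and those without a six-month answer count as users. Remove listwise deletion from it. Keep participants with a missing baseline covariate, by simple baseline imputation or a missing category. Confine respondents-only data to the as-observed sensitivity analysis.
2. **Repair the sensitivity analyses.** Run the multiple imputation unconditionally, with arm and municipality in the imputation model, and describe it as a MAR analysis. Add a delta adjustment that lowers the odds of abstinence among non-respondents from the MAR value towards zero, varied separately by arm, and report the tipping point. This covers the range between MAR and the primary rule, including the mixed corners.

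The cost is revised wording and a few extra model runs. No new data are needed. The wording should be settled before outcomes are analysed.

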## Discussion

This paper describes the study design for evaluating the effectiveness of the U-Niko intervention, a national municipal-based tobacco and nicotine cessation intervention for Danish youth aged 16–25. By integrating insights from field experts, the experiences and preferences of young tobacco and nicotine users, and state-of-the-art research, this intervention aims to serve as an effective supplement to the existing cessation services in Denmark.

The U-Niko intervention is a complex intervention that encompasses three intervention focus areas: training, recruitment, and cessation. Evaluating each focus area independently allows for a nuanced assessment of the intervention’s effectiveness across its focus areas, and ensures that the contribution of each area is captured [28]. If some or all focus areas are shown to be effective, we plan to perform an impact evaluation including cost-effectiveness for the overall intervention and/or effective focus areas. This approach will enable policymakers and practitioners to identify which components are most effective, informing potential scaling and implementation strategies.

The study is a nationwide field trial, extending across the country, counting 55 municipalities from both rural and urban areas of Denmark. This is a great strength, since the intervention will be tested among youths with very different socioeconomic and cultural backgrounds.

Another strength is that it is a field trial and is not driven by researchers. If the intervention activities prove to be effective and municipalities find them helpful, meaningful, and easy to use, they will continue to use them. Thus, there is a high probability of sustainability after the end of the intervention year. By testing the effectiveness of the intervention in 27 different municipal settings, we can acknowledge context-dependent variables, such as social, organizational, political, and economic features, that influence intervention effectiveness [28]. As more than half of the municipalities in Denmark test the U-Niko intervention, it has received great attention, both from not-included municipalities and from Health Authorities.

Because the study is a field trial and the intervention occurs in a real-life setting, there are also some uncertainties regarding the comparison groups, data registration, and follow-up [29]. The youth-oriented cessation activities in the municipalities have been very sparse in the last few years, and there is a risk that only a few young persons will be included in 2025, resulting in too low a power to detect significant differences between the intervention and control municipalities. However, in early 2024, the Danish Health Authorities launched a call in which municipalities interested in improving their work with youth tobacco and nicotine cessation activities could apply for funding. In total, 58 million DKK (~7,7 million euros) were allocated to this work and funding must be used between fall 2024 and 2027. This may have a negative impact on the study, as some municipalities will have a much higher activity level than anticipated. Nonetheless, both the intervention (~44%, n = 12/27) and control municipalities (~54%, n = 15/28) received funding, and therefore, the hopefully positive effect of the increased resources will be present in both the intervention and control groups. Therefore, it should be feasible that the calculated sample size requirements on 27.8 participants during the whole intervention year in each municipality can be accommodated. The analysis of the effectiveness of the U-Niko intervention (recruitment and cessation) will consider that some of the municipalities (more control municipalities) have received extra funding and, therefore, have more resources.

Furthermore, the comparison between municipalities that agreed to participate and those that did not highlights important contextual factors that should be kept in mind when interpreting study findings and considering the external validity of the trial. While both participating and non-participating municipalities had on average the same proportion of youths in the target population, indicating a similar level of need, the municipalities that chose to participate were generally larger, and reported more prior experience with cessation activities. Furthermore, municipalities that participated in the study received higher funding from the Danish Health Authority for youth tobacco and nicotine prevention. However, this funding was announced only after the municipalities had enrolled in the study, and they were informed of their funding status only after randomization had been completed. Nonetheless, these differences suggest that participating municipalities may have had greater capacity to implement and deliver cessation interventions. This raises a concern regarding scalability. Although non-participating municipalities have a comparable youth population and thus similar needs, their more limited resources and experience may pose challenges for implementing the intervention in these settings. This should be considered when interpreting the trial’s potential for broader application.

Another uncertainty is that the municipalities have the responsibility to ensure that each young participant completes the baseline survey and consent form, which can be forgotten, and follow-up surveys may not be prioritized by the young participants. Further, data rely mostly on self-reported measures, which may be subject to reporting biases. However, to motivate higher participation rates in follow-up activities, all youth participants will enter a competition to win a gift certificate for 1000 DKK (~134 euros/139 USD) each time they finish a survey. In total, ten youth (six from the intervention group and four from the control group) will win a gift card. Financial incentives to improve youth survey participation rates are known to be very effective [30], but should be used in a way that will not influence young people’s answers (i.e., only be able to receive the gift certificate if you are tobacco and nicotine-free). Since participating in the competition to win a gift certificate is not dependent on whether the young person is still using tobacco or nicotine, it is anticipated that it will not result in any biases. Furthermore, all youth who state to be tobacco and nicotine abstinent and agree to participate in the cotinine validation after the six-month follow-up will receive a gift certificate for 300 DKK (~40 euros/42 USD) regardless of the test outcome. By offering these incentives to participate in the surveys, it is expected that validity will increase, and fewer young participants will be lost to follow-up.

The U-Niko intervention is resource-intensive, especially due to the face-to-face counseling. Previous studies have shown that low-intensity interventions may be effective. For example, a text message-based cessation intervention targeting youth users of e-cigarettes was shown to be both effective and cost-effective [31]. However, a more recent study suggests that face-to-face counselling yields better cessation outcomes compared to this text-based program, indicating that while digital interventions can be beneficial, in-person support may offer additional advantages in terms of effectiveness [32]. In the development stages of the intervention (S2), both youths who had received cessation counseling and those who had never tried any form of cessation counseling pointed out that face-to-face counseling would have a greater impact on their motivation to quit than online or automated text-generated counseling. With an increasing number of young people using tobacco and nicotine products, there is also a greater demand for effective cessation counseling [1]. Young people have more unassisted quit attempts than adult smokers but have lower success rates [33]. Providing access to cessation support is a key measure in the WHO Framework Convention on Tobacco Control (FCTC) [34]. Therefore, youths who are unable to quit on their own should be offered the help they need and deserve.

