### Intervention

#### Theory of change.

The intervention is tailored to the unique needs of youth users of tobacco and nicotine products. It has been developed based on state-of-the-art research, insights from experienced Danish cessation counselors, and preferences of young tobacco and nicotine users in partnership with Rygestopkonsulenterne ApS (The smoking cessation consultants), a consulting firm with more than 20 years of experience with tobacco and nicotine cessation counseling (S2).

The intervention targets three focus areas:

A) Training of counselors who assist young smokers and nicotine product users to quitB) Recruitment strategy for youth to tobacco and nicotine cessation servicesC) Cessation course for youth who use tobacco and nicotine products.

It is hypothesized that A) counselors trained through U-Niko will report higher skills and confidence in assisting youth quit attempts than those in control municipalities, B) intervention municipalities will recruit more youth into cessation services than controls, and C) youth participating in the intervention municipalities’ cessation services will have higher abstinence rates after six months than those in control municipalities (Fig 3). Furthermore, it is expected that there will be a synergistic effect by optimizing all three areas at the same time.

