### Measures and data assessment

The data assessment is ongoing through 2025 and approx. six months into 2026, includes data on the effectiveness of all three focus areas of the U-Niko intervention and involves seven different data sources (Fig 1). Each focus area of the intervention has its own primary outcome.

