### Data analysis plan

#### A. Training.

A table will present the characteristics of the counselors separately for the intervention and control municipalities, including gender, age, education, years of experience with youth, and experience with tobacco and/or nicotine cessation. The effect of training new youth counselors will be assessed by comparing their self-efficacy scores in the intervention and control municipalities after the intervention year. Because counselors are nested within municipalities, and municipalities are the unit of randomization, a linear mixed-effects model (LMM) with a random intercept for municipalities will be used to account for clustering. The model will be adjusted for counselor characteristics, such as counselor education, years of experience working with youth, and years of experience in tobacco and/or nicotine cessation.

Results from the LMM will be reported as estimated mean differences with 95% confidence intervals (CIs), and a p-value < 0.05 will be considered statistically significant.

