#### B. Recruitment.

A table will present and compare relevant covariates between the intervention and control municipalities, including municipality size, socioeconomic indicators, funding received from the Danish Health Authority, previous experience with youth cessation counseling, and youth population. The effect of the recruitment strategy will be assessed by comparing the number of youths recruited for cessation activities in the intervention and control municipalities using an LMM. The model will be adjusted for relevant covariates, including the number of youths recruited in each municipality in the previous year (2024), municipality size, and whether the municipality received funding from the Danish Health Authority for youth-related cessation activities.

Results from the LMM will be reported as estimated mean differences with 95% CIs, and a p-value < 0.05 will be considered statistically significant.

Secondary results describing the absolute change in the number of youths recruited for cessation activities between 2024 and 2025 in intervention municipalities will be presented using descriptive statistics in a table, with the results shown separately for each municipality.

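### The two-arm design gives three effects of the whole U-Niko package, not the separate contributions of training, recruitment and course that the Discussion promises

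*Protocol article*

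**What the plan says.** The Methods (Theory of change) name three focus areas: A training of counselors, B recruitment and C the cessation course. They add that "it is expected that there will be a synergistic effect by optimizing all three areas at the same time". Under Measures and data assessment, "Each focus area of the intervention has its own primary outcome": counselor self-efficacy, number of youths recruited, and self-reported 14-day abstinence at six months. The subsections on recruitment and cessation label their between-arm comparisons as the effect of the recruitment strategy and of the course respectively.

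The section on the intervention municipalities says that they receive material for all three areas. The section on the control municipalities says that these keep their usual recruitment and cessation services and are offered information on using the U-Niko score.

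The Data analysis plan sets the same threshold for each primary: "confidence intervals (CIs), and a p-value < 0.05 will be considered statistically significant" for training, "mean differences with 95% CIs, and a p-value < 0.05 will be considered statistically significant" for recruitment, and "A p-value < 0.05 will be considered statistically significant" for cessation.

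The Discussion then says that assessing the areas independently "ensures that the contribution of each area is captured". It continues "If some or all focus areas are shown to be effective, we plan to perform an impact evaluation including cost-effectiveness", a sentence that ends by allowing this for the intervention overall and/or for the effective areas. It concludes: "This approach will enable policymakers and practitioners to identify which components are most effective".

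**The concern.** The Discussion moves from three outcomes to three components. A difference in abstinence is read as what the course did, and a difference in recruitment as what the recruitment strategy did. That reading needs municipalities that received one component without the others, and the trial has none.

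The stake is the use to which the results will be put. A municipality or health authority could keep the course and drop the training, or the reverse, on the strength of which primary reached significance. A cost-effectiveness ratio for a single area could set that area's cost against an effect produced by all three.

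**Working it through.** The article gives no figure for the contribution of a component, so the check is whether the design can identify one.

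**Step 1: what was randomized.** 55 municipalities in two arms, 27 intervention and 28 control (Abstract). With components A, B and C each on or off there are 2 × 2 × 2 = 8 possible combinations. The trial observes two: all on, and usual practice. The contrast is not package against nothing, because controls run their own services and are offered information on the U-Niko score, which Table 1 lists under training.

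**Step 2: counting unknowns against contrasts.** For any one outcome, on whatever scale it is modelled (log-odds for abstinence),

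intervention mean − control mean = a + b + c + ab + ac + bc + abc.

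That is 3 main effects, 3 two-way interactions and 1 three-way interaction: seven unknowns and one equation. The interactions cannot be set to zero by assumption, because the article expects synergy.

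**Step 3: in numbers.** Sample size calculations assumes 23% abstinence in control and 34% in intervention municipalities, a difference of 34 − 23 = 11 percentage points. These splits are illustrative and not from the article; each gives exactly 11:

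- course alone 11, everything else 0;
- course 0, training and recruitment together 11;
- 2 each for training, recruitment and course, plus 5 from synergy (2 + 2 + 2 + 5).

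The trial would return the same data in all three cases.

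**Step 4: could each component act only on its own outcome?** That would rescue the component reading, but the article points the other way:

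- Training includes a one-day course in the recruitment strategy, so A feeds outcome B.
- The ICC is justified partly by youths in a municipality sharing a counselor, so trained counselors (A) bear on outcome C.
- Municipalities were randomized in spring 2024, and youths consent at their first cessation contact from January 2025. Recruitment (B) therefore decides who enters the abstinence denominator (C).

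**Step 5: ranking.** The primaries are a mean difference on a 0–30 scale, a mean difference in numbers recruited, and an odds ratio. They share no scale on which one component could be called most effective.

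**Side note on the three thresholds.** The stated 1,526 can be reproduced if two-sided 5% and 80% power are assumed (neither is stated):

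- n per arm = (1.960 + 0.842)² × (0.23 × 0.77 + 0.34 × 0.66) / 0.11² ≈ 261;
- with 20% loss, 261 / 0.8 = 326.25;
- cluster size m = 326.25 × 0.95 / (27.5 − 326.25 × 0.05) = 27.7, or 1,524 youths in 55 municipalities.

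On that reading the sample size carries no multiplicity allowance. If all three null hypotheses are true and the tests independent, the chance of at least one false positive is 1 − 0.95³ = 14.3%. The upper bound is 3 × 0.05 = 15%. With equally correlated tests it is 12.6% at correlation 0.5 and 10.9% at 0.7.

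**The case against.** The strongest reply is that nothing planned is invalid. The comparisons are between randomized municipalities and estimate package effects properly. The article states the expected synergy openly, and an evaluation of the overall intervention is already foreseen. The overlap is also best documented for recruitment and abstinence. The article describes no route by which the course or the recruitment material would alter counselor self-efficacy, although that survey does follow a full year of delivery. All of this stands, and it limits the point to what may be concluded. It does not rescue the claims that each area's contribution is captured or that the most effective component can be identified.

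A reader might go further and infer that the plan needs familywise error control, with a 14% error rate as a defect. The documents do not support that. The three primaries are separately stated hypotheses on different units (counselors, municipalities, youths), each with its own model, and success on some of them triggers only a further evaluation. The 14% also requires all three nulls to be true and the tests independent. Adjustment would not be free either. At 0.05/3, power for abstinence falls from about 80% to about 66% on the reading that reproduces 1,526, and the Discussion already warns of low power.

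A reader might also infer that controls receive none of what the package contains. Their usual services and the U-Niko score information rule that out.

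**Conclusion.** The point holds as one about attribution. The design supports three statements, each about the U-Niko package against usual practice on one outcome. It does not support statements about the contribution, ranking or separate cost-effectiveness of training, recruitment strategy or course. The labels that present the recruitment and abstinence comparisons as effects of the strategy and of the course overreach in the same way.

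This rests on the allocation described in the article and on no numerical assumption. A separate analysis plan could not alter it, because the missing combinations of components were never randomized. The three unadjusted thresholds are a defensible choice for three separate hypotheses and call for no more than a note.

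**What to change.** - In the Abstract, Measures and Data analysis plan, describe the three primaries as effects of the U-Niko package, compared with usual practice, on counselor self-efficacy, number of youths recruited and six-month abstinence. Replace the labels that name the recruitment strategy or the course as the cause.
- In the Discussion, remove the claims that each area's contribution is captured and that the most effective components can be identified. State that separating components would need a design that varies them, such as a factorial one.
- Limit the cost-effectiveness analysis to the overall intervention. Costs may still be itemized by area, but effects cannot be.
- Optionally, note that three primaries are each tested at 0.05, and give the 14% figure with its two conditions and the 15% bound.

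The cost is a more modest claim for policymakers. Randomization, data collection, models, thresholds and sample size are unchanged.
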